### Notifying the GP

Patients will also be asked to give permission to contact their General Practitioner (GP) and inform them about their participation in this study (Annex X). With the patient's permission and written consent, their GP and other doctors involved in their clinical care will be kept informed of their participation in the study. Otherwise, all patient's information will remain confidential, including anything they say in their interview. We may contact their GP to obtain information about their health status if we cannot reach them. A GP letter will be sent to the GPs of all patients taking part in the study. The GPs of family members/friends and nurses will not require to be notified. All information will remain confidential.

## **5. ADVERSE EVENTS**

Due to the nature of the study design, we do not expect any adverse events or serious adverse events. If a participant should experience an event whilst in attendance of the individual interview, standard hospital pathways will be followed, and documentation will be kept in the patient's medical record and filed in the study site file.

Participation in the study may trigger experiences that patients and family members/friends find it difficult to manage. However, it can also be helpful for participants to discuss their feelings within a supportive environment outside of the care context. Throughout this research study, if any incidental findings and/or other patient's safety concerns are identified by the PI, this will be immediately reported to the CI. Following discussion and in agreement with the CI's decision, any participants' safety concerns will be further discussed with the clinical care team.

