### **4.4. WITHDRAWAL CRITERIA**

#### PARTICIPANTS WITHDRAWAL CRITERIA

- No longer willing to participate after consent
- Personal consultee wishing to withdraw participants from the study
- Patients that the clinical and/or research team deem too distressed to continue participating in the study
- Participants who have lost capacity to participate in the study after hospital discharge

For participants wishing to not continue in the research study their decision will be respected. Participants will be reassured that their wishes will not affect their care and/or employment in any way. They will also be informed that they are not required to give a reason with regard to not wishing to participate. However, if they are happy, the reason will be recorded in their medical records.

When conducting clinical research, the study team will always respect participants' interests and prioritise them over those of science and society. Therefore, if the participant wishes to be withdrawn from the study, this must be done without delay and appropriately documented in the medical notes. The research team will respect participants' wishes and feelings by ensuring that no study activities are done to and/or carried out in relation to participants who object to continuing in the study. Those participants wishing to withdraw will be asked for permission to keep the data already collected, but if they decline, all data will be destroyed appropriately.

The study team will also assume the professional responsibility to protect participants from the risk of harm and/or prevent them from feeling pain or discomfort. Additionally, the Principal Investigator in agreement with the Chief Investigator will also consider withdrawing any participant who appears to be in too much distress throughout the research study. If so, this will be discussed with the participant and clearly documented on medical notes.

Participants who lose capacity after hospital discharge or die unexpectedly during the course of the study will be automatically withdrawn. If they are withdrawn, any identifiable data already collected with consent will be retained and may be analysed, but no further data will be collected, or any other research procedures carried out in relation to these patients.

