| 5 | Did the patient look at the digital photo frame during the day?                                     |  Yes  No
If “Yes”, how many times: ____                                                                                                                                                                                     |
| 6 | Did the intervention impact ICU nursing care?                                                       |  Yes  No
If “Yes”, please specify: ____                                                                                                                                                                                     |
| 7 | Was the family intervention delivered without any untoward events (eg., acute distress)?            |  Yes  No
If “No”, please specify: ____                                                                                                                                                                                      |
| 8 | Did the patient request to watch the video more than 3 times a day?                                 |  Yes  No
If “Yes”, please specify the total number of times: ____                                                                                                                                                           |
| 9 | Did the patient develop delirium during the day (8am-8pm)?                                          |  Yes  No
9a. If “Yes”, was the video played again?
 Yes  No
9b. If “Yes”, did it improve delirium status?
 Yes  No |

Table 2. Nursing Checklist Night-time

| N | Nursing Checklist Night-time (8pm – 8am)                          | Tick as appropriate                                                                                                                                                                                                                                                            |

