|----------|-------------------------------------------------------------------|--------------------------------------------------------------------------------------------------------------------------------------------------------------------------------------------------------------------------------------------------------------------------------|
| 1 | Were any visual/auditory aids removed prior to sleep?             |  Yes  No                                                                                                                                                                                                                       |
| 2 | From a nurse’s perspective, how many hours did the patient sleep? | _____ hours                                                                                                                                                                                                                                                                    |
| 3 | Did the patient request to watch the video overnight?             |  Yes  No
If “Yes”, how many times: ____                                                                                                                                                                                     |
| 4 | Did the patient develop delirium overnight?                       |  Yes  No
4a. If “Yes”, was the video played again?
 Yes  No
4b. If “Yes”, did it improve delirium status?
 Yes  No |
| 5 | Was the iPad plugged in to charge overnight?                      |  Yes  No                                                                                                                                                                                                                       |

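### Section 5 ties event documentation to the interviews, day checklist item 7 does not feed into it, and the night checklist has no untoward-event item although overnight video plays are foreseen

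*Protocol*

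**What the plan says.** Protocol Section 5 opens with the expectation that "we do not expect any adverse events or serious adverse events". The procedure that follows is tied to the interview: "If a participant should experience an event whilst in attendance of the individual interview, standard hospital pathways will be followed", with a record in the notes and the study site file. The second paragraph adds a broader clause: "Throughout this research study, if any incidental findings and/or other patient's safety concerns are identified by the PI, this will be immediately reported to the" chief investigator, after which "any participants' safety concerns will be further discussed with the clinical care team". That clause names no form and no filing step.

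Section 6.1 (Study intervention) sets photo display from 8am to 8pm and video plays at 9am, 2pm and 7pm. It adds plays on patient request and a replay when delirium develops, the latter with the personal consultee's agreement. Neither kind of extra play is restricted to daytime.

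Annex XII gives nurses two forms. Table 1 (8am to 8pm) asks in item 7: "Was the family intervention delivered without any untoward events (eg., acute distress", with space to specify if the answer is No. Table 2 (8pm to 8am) asks in item 3: "Did the patient request to watch the video overnight", and in item 4: "Did the patient develop delirium overnight". Item 4a then asks whether the video was replayed, and 4b whether delirium status improved.

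Section 4.4 lists as a withdrawal criterion "Patients that the clinical and/or research team deem too distressed to continue participating in the study".

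**The concern.** The protocol anticipates distress in three places: the withdrawal criteria, the remark in Section 5 that participation may bring up difficult experiences, and day item 7. Yet its written event procedure is attached to the interviews, not to the exposure under study. An untoward event during a video play can be ticked on a form without entering the event record. Between 8pm and 8am it has no field in which to be ticked.

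If the text is followed as written, the final report could state that no adverse events occurred when part of the exposure was never asked about. Feasibility and acceptability are the primary objective (Section 2.1). Distress during a play is direct evidence on acceptability, so incomplete capture would tend to make the intervention look better tolerated than it was.

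**Working it through.** No arithmetic on error rates or sample size applies. The check sets the recording routes side by side and asks what each would capture during delivery in ICU.

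**Item count, Annex XII**
- Table 1 (day): 9 items, of which 1 (item 7) asks about untoward events.
- Table 2 (night): 5 items, covering aids removed, hours slept, video requested, delirium overnight and iPad charging. None asks about untoward events.
- Night items that refer to the video: 2 of 5 (item 3, and item 4 through 4a and 4b).

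The night form therefore foresees plays but does not ask what happened during them. Item 4b is a Yes/No on improvement. A No cannot separate unchanged delirium from a patient who became distressed, and 4b applies only to replays at delirium, not to plays on request.

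**Which exposure falls under which form**
- Scheduled plays (9am, 2pm, 7pm) and photo display (8am to 8pm) all fall within the hours of Table 1, so item 7 covers them.
- Plays on request or at delirium between 8pm and 8am fall under Table 2, with no untoward-event field.

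**Does item 7 reach the Section 5 record?**
- Section 6.1 gives the checklist's purpose as understanding the intervention's impact and whether delirium developed.
- Section 8.4 places completed checklists in individual participant folders.
- Section 5 does not mention the checklist, and Annex XII does not mention Section 5. No text sends a No at item 7 to the medical record and site file.

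**Does the general clause fill the gap?**
- It operates when the principal investigator identifies the concern.
- Section 6.1 has the principal investigator deliver the intervention alongside ICU nurses, so presence at some plays is likely. The Reducing bias text in Section 8 says the principal investigator will not give direct care to participants.
- The principal investigator's hours are not stated, and nothing provides for the principal investigator to observe plays between 8pm and 8am. The nurses complete the forms.

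**The case against.** The strongest reply is that several routes already exist, and most of it stands.

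- A reader might infer that Section 5 covers interviews and nothing else. It does not say that: the clause sending safety concerns to the chief investigator runs throughout the study.
- A reader might infer that harm during exposure cannot be counted at all. That is wrong for all scheduled exposure, which falls within the hours of day item 7.
- A reader might infer that nights leave no trace. Table 2 item 4 records delirium, replay and improvement. Section 6.1 promises close monitoring when a video is replayed at delirium. Withdrawal for distress can be triggered by the clinical team and is documented in the notes. Post-operative complications and delirium-related prescriptions are taken from the records, and the patient, family and nurse interviews discuss the intervention.
- A reader might suppose that replay to a delirious patient at night is where distress is most likely. The protocol contains nothing for or against this.

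These routes reduce the gap but do not close it. Withdrawal captures only distress serious enough to end participation. Complications in the notes are not linked to a play. Interviews depend on recall. The general clause depends on one person becoming aware. None replaces a prompted field completed by the nurse on shift, and none connects item 7 to the event record.

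It is also fair to say that logging every untoward event up to the last follow-up, whatever its relation to the intervention, would be disproportionate. It would sweep in ordinary complications of cardiac surgery that Section 6.1 already collects. The correction should stay with intervention delivery.

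**Conclusion.** The concern holds in a limited form. Section 5 attaches its documentation procedure to the interviews, day item 7 is not connected to it, and the night form lacks the equivalent item despite foreseeing plays.

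The size is one missing item on one of two paired forms and one missing link between form and procedure. The number of events that could be lost cannot be estimated, because the protocol gives no figure for night requests or night delirium. The scheduled daytime plays are not a measure of the gap, since item 7 covers them. The direction is clear: incomplete capture understates untoward events and favours acceptability.

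This rests on two assumptions: that some plays do occur between 8pm and 8am, as Table 2 itself anticipates, and that the Annex XI and Annex XIV diagrams, which are not available in the text reviewed, contain no event-recording step. The point does not depend on any analysis plan, because the event procedure and the nurse forms are fixed in the protocol.

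**What to change.** 1. Repeat day item 7 in Annex XII Table 2, with the same free-text field and a not-applicable option for nights when no video was shown.
2. Extend the Section 5 documentation procedure (medical record and site file) to untoward events during or following intervention delivery in ICU. State that a No at day item 7 or its night counterpart is entered through that procedure.
3. Report the number of patients with at least one such event, alongside the number withdrawn for distress, with the acceptability results.

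These changes concern recording and reporting only. How an event is managed clinically stays with the care team.

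The cost is one item on an existing form, a sentence or two in Section 5, slightly more nurse time at night, and the amendment steps that Section 9 already describes.

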## **6. STUDY ASSESSMENTS**

### **6.1. ASSESSMENT AND FOLLOW UP**

#### **STUDY INTERVENTION**

The intervention will require family members/friends (selected by patients) to self-record short videos (during the preoperative stage) based on a carefully drafted guided script divided into two parts: a) Reorientation (discussing date/time/surroundings, family members on the video); b) Reassurance (providing comforting/supportive messages). Videos will be recorded either with a video-recorder device (provided by the research team) in the pre-operative clinic or at home using a personal smartphone. At a later stage, videos will be sent to an encrypted NHS email and securely uploaded in line with ICHT Information Governance to a password-protected iPad, which will also facilitate family-patient video calls in ICU. In addition, patients will be requested to select personal pictures pre-operatively, which will be also sent to the PI's encrypted NHS email and securely uploaded into a special digital photo frame with reference to time and date.

Digital photos will be shown continuously at the patient's bedside for 12 hours a day (between 8am to 8pm) and different family videos will be played three times at specific hours of the day (9am, 2pm and 7pm) throughout their stay in ICU. Additionally, videos will be also played upon patient request and last video shown that day will be re-played. In occasions when patients develop ICU delirium and considering personal consultee's agreement, the last video shown to participants will be re-played and patients will be closely monitored. This will help the research team to understand if the combination of personal pictures and family videos impacted patients' orientation and reassurance and if, ultimately, promoted the reduction of ICU delirium. The PI will be responsible for setting up the required equipment and delivering the intervention alongside ICU nurses as illustrated in the study diagram below (Annex XI).

The draft guided script of reorientation and reassurance messages was initially developed based on published research and considering patients' memories from their lived ICU experience(s) [15]. Subsequently, it was further refined within a lay focus group of patient and public members (with ICU lived experience) and reviewed by an expert panel comprising two critical

care consultants, two critical care nurses and one clinical academic research nurse (Annex XIII). Family members and friends will be requested to not deviate from the draft script order of events and to frequently mention the patient's name at the beginning/end of sentences when recording the video. They will be also asked to provide personalised messages in the second part of the video and to use simple terms equivalent to a 5th-grade reading level. The research team expects that part A) of the video to be similar between study participants, but part B) tailored to each individual participant.

Additionally, as previously agreed and supported by the critical care nursing lead for the ICU at Hammersmith Hospital, all critical care nurses will contribute to the study by filling in a daily checklist (Annex XII). This checklist will help the research team to understand the impact of the study intervention and if participants developed ICU delirium. Moreover, as per standard ICU practice at ICHT, patients following cardiac surgery will be closely monitored and primary outcomes regularly collected by critical care nurses.

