### **1.1. BACKGROUND**

Delirium is a common and often undiagnosed brain dysfunction that occurs in ICU and is associated with increased morbidity and mortality [1,2]. Its incidence can vary between 30-80% depending on various risk factors, doubling the National Health Service (NHS) inpatient cost per patient compared to those without delirium [3,4]. It is a complex, distressing and debilitating condition that impacts patients, family members and healthcare professional [5].

Patients undergoing cardiac surgery are a particularly vulnerable group as ICU delirium affects up to 55% of these patients, due to operative reasons including surgical complexity and cardiac bypass time [6,7]. Delirium is associated with increased anxiety and depression, poor functional status, increased risk of stroke and significant cognitive impairment up to a year post-cardiac surgery. It has also been linked with an elevated number of hospital readmissions, longer ICU and hospital lengths of stay [8,9].

Given the significant burden on patients and the NHS, delirium prevention and management is considered to be national priority in ICU by the James Lind Alliance [10]. Delirium is potentially preventable and healthcare professionals must diagnose this condition in critical care units by using the Confusion Assessment Method (CAM-ICU) screening tool as per the UK National Institute for Health and Care Excellence (NICE) guidelines [11,12]. Whilst pharmacological interventions are the mainstay of treatment in ICU, the Society of Critical Care Medicine highlights the importance of non-pharmacological therapies in the management of ICU delirium [2]. Therefore, there is an urgent unmet need to identify novel non-pharmacological management strategies to prevent and treat ICU delirium [10].

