## **3. STUDY DESIGN**

The study will be conducted over twelve months in the Cardiac Intensive Care Unit at Hammersmith Hospital, Imperial College Healthcare NHS Trust. For this study, a total of 30 individuals (12 patients, 12 family members or close friends and 6 critical care nurses) will be recruited and interviewed to allow sufficient depth and richness of data. Patients and family members/friends will be mainly recruited from the ICHT pre-operative clinic outpatient department, which runs several pre-operative clinics per week. Each week, approximately eight patients undergo cardiac surgery, and the research team intends to recruit one patient and their family member/friend per a week for a period of 4 months.

All participants will be given time to consider their participation in the study and if happy will be consented by PI or other delegated member of the research team. Patients will be approached during one of their pre-operative clinic appointments and informed consent will be sought at this stage. Once written consent has been obtained, patients will be asked to nominate a family member or friend to be contacted by the PI. After signing the consent form, family members/friends will also be enrolled into the study and requested to self-record short videos pre-operatively (based on a guided script - ANNEX XIII), which will be safely uploaded to an iPad. In addition, patients will be requested to select multiple pictures, which will be securely uploaded into a digital photo frame. This package combination of videos and pictures will be shown to patients post-operatively in ICU. Critical care nurses will be recruited after they have provided direct care to at least one participant, who received the study intervention in ICU.

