This is a mixed methods research study including the collection of data from patient's medical notes, interviews and quality of life questionnaires in accordance with the schedule of assessments (SoA, Annex I). This study also involves the implementation of an auditory-visual sensory stimulation package in the cardiac ICU at ICHT to participants enrolled in the study. Digital photos will be shown continuously at the patient bedside after cardiac surgery and will always have reference to time and date. Additionally, videos will be played throughout participants' stay in ICU for at least three times per day and upon participant request. Videos will be also played when participant show signs of ICU delirium with the aim of reducing delirium incidence and improve overall better health outcomes. Simultaneously, primary outcomes measures (CAM-ICU, a routine delirium screening measure) will be collected by the research team, as this is evaluated twice a day as per usual standard of ICU practice, with the aim of assessing whether patients develop delirium during their stay in ICU.

Interviews with patients and families/friends will be held in three different occasions. The first one will be on the same day as ICU discharge, the second interview will be on the day of hospital discharge and the third one will be carried out up to a month following hospital discharge during their clinical follow-up appointment. Where possible, family members/friend and patient's interviews will be conducted together (dyadic interviewing), but the possibility of performing interviews separately will be given, so that participants feel able to discuss opinions freely without influence. Nurses' interviews will be held as a one-off and after they have provided direct care to participants who received the proposed intervention.

Each patient will be followed up daily on the wards and once at the monthly follow-up clinic up after ICU discharge, where cognitive and emotional assessments will be performed to evaluate delirium outcomes. The research team will also collect relevant information from participant's medical notes if any complications post ICU discharge arise during inpatient and follow-up stages.

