## ANNEX XII – Critical Care Nurse’s checklist

Table 1. Nursing Checklist Daytime

| N | Nursing Checklist Daytime (8am – 8pm)                                                               | Tick as appropriate                                                                                                                                                                                                                                                            |
|----------|-----------------------------------------------------------------------------------------------------|--------------------------------------------------------------------------------------------------------------------------------------------------------------------------------------------------------------------------------------------------------------------------------|
| 1 | Did the patient have any unknown visual/auditory impairment?                                        |  Yes  No                                                                                                                                                                                                                       |
| 2 | Were any visual/auditory aids (eg. glasses/hearing aids) in place during the intervention delivery? |  Yes  No  N/A                                                                                                                                                                                          |
| 3 | Was the family intervention delivered 3 times during the day (8am-8pm)?                             |  Yes  No
Times: 1. ____:____; 2. ____:____; 3. ____:____                                                                                                                                                                    |
| 4 | Did the patient express any verbal/non-verbal emotions when watching the video?                     |  Yes  No
If “Yes”, please specify: ____                                                                                                                                                                                     |

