#### **A) Reorientation**

- Start the video by greeting the patient and mentioning their name.
- Introduce yourself (e.g., name/preferred name) and your relationship to the patient.
- State where you are (e.g., house, garden, etc.) and if you are alone or accompanied (e.g., with significant others, pets, special objects/toys)
- Mention the patient's name in the beginning/end of the next sentences
- Provide a reference to the approximate time (9am, 2pm or 6pm) and date (e.g., Wednesday)
- Mention that patients have now had their surgery and are staying in Intensive Care at Hammersmith Hospital in London.
- State how many days have been since surgery (e.g., today is day 1 after your cardiac surgery)

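### Day-specific videos are all recorded before an ICU stay of unknown length, and the checklist cannot tell a slot with no valid video from a missed or wrong-day play

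*Protocol*

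**What the plan says.** **Frequency and duration.** Section 6.1 (Study intervention) states that "different family videos will be played three times at specific hours of the day (9am, 2pm and 7pm) throughout their stay in ICU". Section 3 gives a similar rule without the word different: "videos will be played throughout participants' stay in ICU for at least three times per day and upon participant request". Annex I places the ICU family intervention in columns D1, D2 and D3 only, with the ward period starting at D4.

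**Recording.** Section 3 has relatives "requested to self-record short videos pre-operatively", and section 6.1 repeats that they "self-record short videos (during the preoperative stage"). Section 4.6 allows recording at the consent visit, at another hospital appointment before the operation, or at home. Section 4.5 lists the surgery date among the pre-screening data as provisional.

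**Content.** Part A of the Annex XIII script asks relatives to "Provide a reference to the approximate time (9am, 2pm or 6pm) and date (e.g., Wednesday") and to "State how many days have been since surgery (e.g., today is day 1 after your cardiac surgery"). Section 6.1 and Annex XIII ask relatives to keep to the script's order. Annex XIII sets the length of a video at 3 minutes.

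**Replay.** Section 6.1 allows the last video to be shown again at the patient's request or when delirium develops. Section 4.6 repeats the delirium rule.

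**Delivery record.** Daytime item 3 of the Annex XII checklist asks "Was the family intervention delivered 3 times during the day (8am-8pm"), with a Yes/No box and three spaces for clock times.

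**The concern.** A video that names its day and weekday fits one postoperative day. If such videos are needed for every ICU day, the number required depends on a length of stay that nobody knows when the relative records them. The protocol then asks for something that a fixed set made beforehand cannot guarantee.

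Feasibility is the primary objective (section 2.1), and item 3 is the checklist question on whether the scheduled plays took place. Two feasibility problems can occur here: the family's material may not cover the stay, or the material exists and is not played at the bedside. They call for different remedies in a later trial, and item 3 merges them. A third possibility is that the slot is filled with a video announcing the wrong day, which runs against the purpose of the reorientation part.

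Section 1.1 associates delirium with "longer ICU and hospital lengths of stay". If that holds here, the ambiguous entries would tend to come from the patients of most interest.

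**Working it through.** The protocol's visible text gives neither a number of videos nor an ICU length-of-stay figure, so it has no figure to reproduce. The check is a count, followed by a comparison of what item 3 would contain.

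**Inputs from the protocol**
- 3 scheduled slots per ICU day (section 6.1; a minimum in section 3)
- 3 minutes per video (Annex XIII)
- 3 intervention columns, D1 to D3 (Annex I)

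**Assumptions, not in the protocol**
- Supply S = 9 videos, which is 3 × 3 for D1 to D3
- ICU intervention days d = 3, 4, 5 and 7, chosen to show the pattern

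**Formulas**
- Videos needed = 3d
- Slots without a day-valid video = max(0, 3d − S)
- Share = that number ÷ 3d

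| d | Needed | Minutes of video (3 × needed) | No day-valid video, S = 9 | Days with item 3 Yes, if run-out days are entered No | Days with item 3 Yes, if replays are entered Yes |
|---|---|---|---|---|---|
| 3 | 9 | 27 | 0/9 (0%) | 3/3 | 3/3 |
| 4 | 12 | 36 | 3/12 (25%) | 3/4 | 4/4 |
| 5 | 15 | 45 | 6/15 (40%) | 3/5 | 5/5 |
| 7 | 21 | 63 | 12/21 (57%) | 3/7 | 7/7 |

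**Range over the assumed supply.** With S = 15 (five days' worth) the share is 0 at 4 and 5 days and 6/21 (29%) at 7. With S = 3 (one day's worth) it is 9/12 (75%), 12/15 (80%) and 18/21 (86%) at 4, 5 and 7 days. For any S, a shortfall appears once d exceeds S/3. The size depends on S; the existence of a limit does not.

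**Weekday.** The count tests only the day number. If the operation moves by anything other than whole weeks, a weekday recorded beforehand is wrong on every ICU day, including D1 to D3, although the day number stays right. The protocol does not say whether the date is firm when recording takes place, so this is not in the table.

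**What item 3 would hold**
- Valid videos exist but are not played: No.
- The set is used up and nothing is played: No.
- Three videos matching the day are played: Yes, with three times.
- The set is used up and an older video is played three times: Yes, with three times.

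The first two give the same answer, and so do the last two. Item 3 has no space for a reason, whereas items 4, 6 and 7 do. No other day or night item asks which video was played or whether one existed. The replay rules cover patient request and delirium, not a scheduled slot.

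**The case against.** **The number of videos may be stated elsewhere.** Section 6.1 refers to the Annex XI delivery diagram, which is not visible, and the family information sheet (Annex IV) is not reproduced. This stands: one cannot say that the plan gives no number. It does not remove the problem, because any fixed number can be outlasted.

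**Different may mean only that the three daily slots differ, with the same three videos reused each day.** Section 3 omits the word, so the reading is possible. The script's day and weekday lines speak against it. If it was intended, section 6.1 and Annex XIII still conflict, because from day 2 each reused video names the wrong day.

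**Annex I limits the intervention to D1 to D3, so nine videos suffice.** If Annex I governs, run-out disappears, and a family load without limit should not be inferred. Sections 3 and 6.1 nevertheless say the whole ICU stay, and this contradiction is part of the point.

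**A reader might infer that the shortfall is scored as non-delivery, and that delivery will therefore look worst in delirious patients.** The documents support neither. Item 3 counts plays, so a replay can be ticked Yes and recorded delivery can stay complete. Section 1.1 offers only a general background association, and section 7 defines no delivery proportion.

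**The study has other ways to learn of the problem.** The investigator uploads the videos and helps to deliver them, so the team knows the supply at the time. Nurse interviews cover limitations, and section 9 provides for deviation forms. These may reveal that videos ran out, but they do not classify individual slots. Section 8.4 deletes the videos from the devices at ICU discharge, so an unlogged count may be hard to recover.

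**Conclusion.** The concern holds in this form: sections 3, 4.6 and 6.1, Annex I and Annex XIII cannot all be followed when a stay outlasts the recorded set, and item 3 leaves the record of such slots undefined. The error can go either way. In the illustration, days recorded as fully delivered could be anywhere from 3/4 to 4/4 at 4 ICU days, 3/5 to 5/5 at 5, and 3/7 to 7/7 at 7, for the same supply.

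The shares of 25%, 40% and 57% are correct arithmetic on an assumed supply of nine and chosen stays. They are not forecasts. Without a length-of-stay figure, the number of the 12 patients affected is unknown and could be zero. The structural conclusion rests only on the pre-operative recording, the day-specific script and the whole-stay rule. It is a modest defect, worth correcting because the remedy is cheap and the quantity concerned bears on the primary objective.

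**What to change.** 1. Reconcile sections 3, 4.6 and 6.1, Annex I and Annex XIII on three matters: whole ICU stay against D1 to D3, a day-numbered script against recording before surgery, and what the plan intends for a scheduled slot without a day-valid video. The evening time also differs (7pm in section 6.1, 6pm in Annex XIII) and can be settled in the same edit. Which schedule is right is for the investigators.
2. Log two fields per patient: the number of videos supplied and the last postoperative day that they cover.
3. Under daytime item 3, add a coded answer for *no day-valid video available*, and record whether the video played matched the day.
4. Report two figures: slots played with a matching video ÷ slots that had a valid video (bedside delivery), and slots without a valid video ÷ scheduled slots (supply shortfall). In the 5-day illustration, if every valid slot was used, these are 9/9 and 6/15. A single slot-level figure could be 9/15 or 15/15, depending on how run-out slots were entered.

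The cost is a text edit, an extra option and a day-match entry on the checklist, a two-field log for 12 patients, and two delivery figures instead of one.
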